## Results

This study was funded in 2023 by the Fundación Progreso y Salud (reference AP-0429‐2023-C4-F2). Participant recruitment was conducted between November 1, 2025, and December 31, 2025. As of January 2026, 35 of the planned 70 participants had been recruited. Data collection for all outcome measures is expected to be completed by March 31, 2026. Data analysis, interpretation, and manuscript preparation will be carried out during 2026. The results of the trial are expected to be submitted for publication in late 2026.

## Discussion

### Comparison With Prior Work

Due to the increasing prevalence of musculoskeletal diseases, such as cervicalgia, and their socioeconomic impact globally [8-10], the importance of finding increasingly cost-effective and evidence-based treatment options for the approach increases. CNSNP is frequently associated with musculoskeletal disorders, including decreased strength and endurance of the deep cervical muscles, range of motion restrictions, postural disturbances, and peripheral and central sensitization [50,51].

EDN and therapeutic exercise are minimally invasive techniques used in the treatment of musculoskeletal pain, including chronic neck pain. EDN combines dry needling with electrical stimulation, seeking to enhance its analgesic and muscle relaxation effects [23,24]. Specific therapeutic exercise targeting the cervical region has been shown to be one of the most effective interventions for reducing pain intensity and functional disability in this population [13,15]. This type of exercise seeks to improve activation and motor control of the deep cervical muscles, restore the support and stabilization function of the cervical spine, and increase muscle strength and endurance, which contribute to improved load-bearing capacity and pain reduction. Furthermore, exercise promotes joint mobility, local circulation, and central nervous system modulation, generating both peripheral and central effects on pain perception [18,19,52].

Although both techniques are used in clinical practice and there are studies supporting their use, there is still no conclusive evidence directly comparing their efficacy and safety in patients with CNSNP. Comparing these 2 interventions with isolated therapeutic exercise can provide valuable information to determine which offers better results in terms of pain reduction, functional improvement, quality of life, and safety.

Therefore, this clinical trial emerges as a necessity to fill this gap in the evidence base, enabling more informed and evidence-based decision-making by health care professionals caring for patients with CNSNP. Furthermore, the results could contribute to optimizing treatment protocols and improving clinical outcomes in this population.

### Strengths, Limitations, and Contingency Plans

One of the main advantages of this protocol is that it is not intended to replace traditional rehabilitation but rather to provide complementary and/or parallel treatments in order to achieve more effective outcomes over time.

The main difficulties and limitations of the protocol include maintaining participant adherence throughout the course of the study, the impossibility of blinding both participants and physiotherapists—which could introduce bias—and the inability to control external aggravating factors of the pathology, such as high workload, elevated stress levels, among others. In addition, a sham EDN or attention-control intervention was not included in the study design. Therefore, nonspecific effects related to therapist contact time, patient expectations, or contextual factors cannot be completely excluded when interpreting the study findings. Consequently, the study will evaluate the effectiveness of adding EDN to usual exercise-based care rather than isolating the specific physiological effects of EDN itself. Accordingly, any observed between-group differences should be interpreted with caution, as they may reflect both specific intervention effects and nonspecific contextual influences.

Nevertheless, to facilitate adherence and minimize dropouts during the study, participants will receive reminders by phone call or WhatsApp regarding the date and time of each session. In addition, patients will be periodically informed of their improvements and progress, with the aim of motivating them to remain engaged in the treatment.

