**Figure 1. F1:**
[figure not shown]
Schedule of participants and intervention characteristics. CROM: cervical range of motion; MTrPs: myofascial trigger points; NDI: Neck Disability Index; PCS: Pain Catastrophizing Scale; PSQI: Pittsburgh Sleep Quality Index; SF-36: Short Form-36 Health Survey; TSK: Tampa Scale of Kinesiophobia; VAS: Visual Analog Scale.

To improve treatment fidelity and intervention standardization, all physiotherapists involved in the study will receive prior training regarding intervention delivery, outcome assessment procedures, and adverse event reporting. Standardized treatment records and session checklists will be used throughout the study.

Participants were not directly involved in the design or conduct of this trial. However, feedback regarding feasibility, acceptability, treatment burden, and participant satisfaction will be collected during follow-up visits to inform future clinical research and implementation strategies.

To ensure participant safety and sample homogeneity, exclusion criteria were operationally defined prior to recruitment. Severe cervical pathology was defined as cervical myelopathy, progressive cervical radiculopathy with neurological deficits, fracture, tumor, inflammatory cervical disease, severe cervical stenosis, or other red-flag conditions requiring medical management. All participants underwent a standardized clinical screening based on current neck pain clinical practice guidelines before enrollment. History of spinal surgery was defined as any previous cervical spine surgical procedure, including decompression, discectomy, fusion, arthroplasty, or stabilization surgery. Coagulation disorders included diagnosed bleeding disorders or conditions requiring special precautions for needling procedures [4,28-30]. Prior to enrollment, all participants will undergo a standardized screening examination performed by a physiotherapist and confirmed by a rehabilitation physician when necessary. Screening will include medical history, neurological examination, assessment of red flags for serious spinal pathology, and review of available imaging reports when clinically indicated (Textbox 1).

Textbox 1.Inclusion and exclusion criteria.

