To minimize treatment variability, all therapists will follow a standardized intervention manual detailing patient positioning, trigger point identification, needle placement procedures, stimulation parameters, and safety precautions [31,32,35]. A treatment record form will be completed after each session documenting the muscles treated, number of needles inserted, stimulation intensity, treatment duration, and any adverse events.

Participants will be informed about the possibility of postneedling soreness and will be instructed to apply local cryotherapy if required during the first 48 hours. A follow-up telephone call will be conducted 48 hours after each treatment session to monitor adverse events and ensure participant safety.

Immediately after EDN, participants will perform the same cervical-specific therapeutic exercise program received by the control group. Therefore, this trial is designed to evaluate the added value of incorporating EDN into an exercise-based physiotherapy program rather than isolating the specific physiological effects of EDN itself.

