### Data Collection and Outcome Measures

At the start of the study, demographic and clinical data will be collected, and all outcome measures will be assessed at 3 time points: baseline (preintervention), immediate posttreatment (1 d after the last session), and short-term follow-up (2 mo postintervention). Outcome assessments will be performed by a blinded evaluator using standardized procedures and calibrated instruments to improve measurement reliability and reproducibility.

The primary outcome is the Neck Disability Index (NDI), a 10-item questionnaire assessing activities of daily living. Each item is scored on a 0‐5 Likert scale. Total scores are converted to percentages (0%‐100%), with 0% indicating full independence and 100% indicating complete dependence [38,39].

Secondary outcome measures include the following:

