### Randomization

Participants will be randomly assigned to either the experimental group (EDN plus therapeutic exercise) or the control group (therapeutic exercise alone) using a computer-generated randomization sequence created by an independent statistician.

Allocation concealment will be ensured using sequentially numbered, opaque, sealed, tamper-evident envelopes prepared by an independent researcher not involved in participant recruitment, outcome assessment, or treatment administration. Envelopes will be opened sequentially only after completion of the baseline assessment and immediately before the first intervention session.

The outcome assessor will remain blinded to group allocation throughout the trial. Participants and treating physiotherapists cannot be blinded due to the nature of the interventions.

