The primary end point will be the between-group difference in change in NDI scores from baseline to postintervention. Postintervention was defined as 1 day after completion of the sixth treatment session. Age, sex, and baseline NDI values will be explored as potential covariates if baseline imbalance is detected. Secondary outcomes will include changes in Visual Analog Scale, McGill Pain Questionnaire, quality of life SF-36, Tampa Scale of Kinesiophobia, cervical range of motion, Pittsburgh Sleep Quality Index, PCS, pressure pain threshold, cervical isometric strength, and cervical flexor endurance. Effect sizes (eg, Cohen *d*) will be calculated to assess the magnitude of differences.

Additionally, the clinical relevance of the findings will be assessed by comparing observed changes with established minimal clinically important differences. Based on previous studies in patients with neck pain, a change of approximately 7.5 points on the NDI and 1.5 points on pain intensity scales has been considered clinically meaningful and will be used to aid the interpretation of clinical relevance [49]. For other secondary outcomes, where established minimal clinically important differences are available, these will be considered to aid the interpretation of clinical significance.

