### Safety Considerations

All patients and physiotherapists will receive specific information about the study in writing and will have a chance to discuss the procedures with a member of the study team before providing consent to participate. They will also be informed that they can withdraw from the study at any time. Participants who agree to participate in the study will sign 2 copies of the informed consent form, one that will be kept in the trial records and one for the participant.

The data collected from each patient will be stored in a closed locker in an office at the University of Almería, and only the physiotherapists evaluators will have access to that information. Subsequently, the data will be entered and saved by the statistician on a password-protected laptop to maintain confidentiality. Eligibility criteria, results, and analyses will not be modified after registration of the first participant.

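### The 48-hour adverse event call is described only for the EDN arm, so a between-arm safety comparison would rest on unequal ascertainment; progress feedback before the NDI is a smaller, related point

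*Protocol article*

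**What the plan says.** **Adverse events.** The section on the EDN plus exercise group says: "A follow-up telephone call will be conducted 48 hours after each treatment session to monitor adverse events and ensure participant safety". The sentence follows directly on the advice about soreness after needling. The section on the exercise group, including Table 1, describes the exercise programme and no telephone call. The section on adverse event monitoring applies to both arms: treating physiotherapists record events throughout, and participants are encouraged to report symptoms. Table 2 ticks adverse event monitoring at each of the six sessions and at the 2-month visit. Weekly reminders by phone, email or WhatsApp go to all participants (Randomization, Treatment Allocation, and Adherence), but they concern attendance. Under Comparison With Prior Work, safety is listed among the aspects on which the comparison should inform.

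**Progress feedback.** The section on strengths and limitations says that "patients will be periodically informed of their improvements and progress, with the aim of motivating them to remain engaged in the treatment". The Randomization section says: "Participants and treating physiotherapists cannot be blinded due to the nature of the interventions". The outcome section says: "The primary outcome is the Neck Disability Index (NDI), a 10-item questionnaire assessing activities of daily living". The Data Analysis section says: "The primary end point will be the between-group difference in change in NDI scores from baseline to postintervention", with postintervention set at 1 day after the sixth session.

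**The concern.** The number of adverse events found depends on how often and how actively one asks. If one arm is telephoned two days after every session and the other is not, a difference in recorded events mixes a difference in harm with a difference in asking. The events the protocol itself expects, a temporary increase in pain and bruising, are minor and may have passed by the next weekly visit, so they are the ones most sensitive to an extra call. At stake is the fairness of any statement about the relative safety of adding EDN.

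The feedback raises a different question. Assessor blinding does not mask the person whose answers make up the NDI. Telling that person about improvement before the primary questionnaire is an avoidable influence on a subjective score, separate from the unavoidable lack of blinding.

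**Working it through.** The plan gives no adverse event figure to reproduce. The only arithmetic is a count of contacts; the rest is a comparison of sections.

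**1. Scheduled occasions on which adverse events are asked about or recorded, per participant**

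| Source | EDN + exercise | Exercise alone |
|---|---|---|
| Sessions (Table 2) | 6 | 6 |
| 2-month visit (Table 2) | 1 | 1 |
| 48-hour calls (EDN section) | up to 6 | none described |
| Total | up to 13 | 7 |

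At the planned 35 per group this is up to 6 × 35 = 210 calls in the EDN arm and 0 × 35 = 0 in the exercise arm. These are contacts, not events.

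**2. Direction of the effect.** Let p be the true proportion with an event and d the probability that an event is recorded. Then

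recorded ratio = (p_EDN × d_EDN) / (p_Ex × d_Ex) = true ratio × (d_EDN / d_Ex).

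If the shared monitoring works equally well in both arms and a call can only add to detection, then d_EDN / d_Ex is at least 1 and the recorded ratio moves towards more events with EDN. The documents give neither d, so the size of the factor cannot be derived.

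**3. The period after session 6.** The postintervention assessment is 1 day after the last session, and the sixth call would come at 48 hours. After that assessment the exercise arm has no scheduled contact until the 2-month visit and depends on spontaneous reporting. The imbalance is therefore not confined to the weeks between sessions.

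**4. Feedback and the primary outcome.** The stated aim of keeping patients engaged in treatment places the feedback during the six weeks, before the primary NDI. Table 2 schedules no outcome assessment between baseline and session 6, so the source of the progress information is not stated. The sentence refers to patients in general. If feedback shifts NDI reporting by s_EDN and s_Ex, the between-group difference is biased by s_EDN − s_Ex, which is zero when the shifts are equal. The documents give neither shift. They support a risk to the NDI contrast, not a demonstrated bias.

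**The case against.** The strongest reply on adverse events is that the call is a sensible safety contact after an invasive procedure, that no sentence says control participants are not called, and that the control arm is not left to chance: sessions, checklists, training and encouragement to report apply to everyone. Adverse events are neither a primary nor a secondary outcome, no between-arm test is planned, and the mention of safety is Discussion prose. This limits the consequence and leaves open that one clarifying sentence settles the matter. It does not make the described procedures equal, and a descriptive table by arm would carry the same imbalance as a test.

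On feedback, the reply is that it covers both arms, may be no more than a therapist's encouragement on a progressive programme, and falls under the expectation and context effects already conceded as limitations. Most of that stands. What remains is that the protocol presents statements about improvement as an adherence aid and does not name them as a source of bias.

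A reader might go further and infer that assessor blinding is compromised, because "feedback regarding feasibility, acceptability, treatment burden, and participant satisfaction will be collected during follow-up visits" and, for stored data, "only the physiotherapists evaluators will have access to that information". The documents do not support this. They do not say that the assessor collects the feedback, nor that needling or session records are in the assessor's files. The Masking section tells participants not to disclose their treatment and has the assessor's guesses of allocation reported.

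**Conclusion.** The point holds for adverse event ascertainment. As described, active solicitation after each session exists in one arm only, up to six calls per participant against none, and a between-arm safety comparison would be biased towards more events with EDN. This rests on two readings: that the placement of the call under the EDN heading, with silence in the exercise section, means what it appears to mean; and that the shared monitoring performs alike in both arms. Neither a multiple for the apparent excess of events nor a number of NDI points can be supported; any such figure would be an assumption restated.

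The feedback point is secondary. A reader might infer that feedback inflates the NDI difference in favour of EDN. The text applies it to both arms and schedules no interim NDI that could be fed back, so a differential effect is not shown. The sample size and the primary analysis model need no change.

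**What to change.** **Participants still to be treated.** Ask the same scripted adverse event question, by the same mode and at the same times, in both arms. The weekly reminder contact that all participants already receive could carry it, with one matching contact after session 6. Leave the EDN safety call as described, and record for each event how it came to light. If control participants are in fact called, say so in the exercise section.

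**Participants already treated.** The article reports 35 recruited as of January 2026 and expected data collection to end in March 2026, so this may be the part that applies. Base the between-arm comparison on events recorded at the scheduled sessions and the 2-month visit in both arms, and report call-elicited events separately. This reduces the imbalance without fully removing it, since an event discussed by telephone may be more readily noted at the next session; state that with the results.

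**Feedback.** Before the last assessment, limit contacts to neutral reminders and adherence encouragement without statements about outcome improvement, or script them identically in both arms. For those already treated, disclose the feedback as a limitation.

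**Cost.** A brief added question in control-arm contacts, a source field on the adverse event form, and the loss of one motivational tool; schedule cards and reminders remain. A change made midway would make ascertainment differ over time, so its date should be documented.
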